## Abstract

**Background:**

Tailored psychosocial activity-based interventions have been shown to improve mood, behaviour and quality of life for nursing home residents. Occupational therapist delivered activity programs have shown benefits when delivered in home care settings for people with dementia. The primary aim of this study is to evaluate the effect of LEAP (Lifestyle Engagement Activity Program) for Life, a training and practice change program on the engagement of home care clients by care workers. Secondary aims are to evaluate the impact of the program on changes in client mood and behaviour.

**Methods/design:**

The 12 month LEAP program has three components: 1) engaging site management and care staff in the program; 2) employing a LEAP champion one day a week to support program activities; 3) delivering an evidence-based training program to care staff. Specifically, case managers will be trained and supported to set meaningful social or recreational goals with clients and incorporate these into care plans. Care workers will be trained in and encouraged to practise good communication, promote client independence and choice, and tailor meaningful activities using Montessori principles, reminiscence, music, physical activity and play. LEAP Champions will be given information about theories of organisational change and trained in interpersonal skills required for their role. LEAP will be evaluated in five home care sites including two that service ethnic minority groups. A quasi experimental design will be used with evaluation data collected four times: 6-months prior to program commencement; at the start of the program; and then after 6 and 12 months. Mixed effect models will enable comparison of change in outcomes for the periods before and during the program. The primary outcome measure is client engagement. Secondary outcomes for clients are satisfaction with care, dysphoria/depression, loneliness, apathy and agitation; and work satisfaction for care workers. A process evaluation will also be undertaken.

**Discussion:**

LEAP for Life may prove a cost-effective way to improve client engagement and other outcomes in the community setting.

**Trial registration:**

Australian New Zealand Clinical Trials Registry ACTRN12612001064897.

## Background

Aged care will increasingly be provided at home rather than in institutions [1,2]. This trend is driven by the wishes of older people to stay at home [3-6], and changing social structures reducing the availability of informal family care. Although desirable, there are negative aspects to living at home as an older person. A third of community dwelling older persons have reported being lonely, most of these (80%) did not receive home visitation or telephone contact services, and 40% did not attend any group activities [7]. Community dwelling older persons have also reported having limited access to meaningful activities [8]. Older people who receive home care (also known as community or domiciliary care) services want personalised activities and opportunities for socialisation [3]. The most frequent unmet needs of persons with dementia living alone were daytime activities (54%), company (52%), and care for psychological distress (44%) [9,10]. Home care recipients’ ratings of their opportunities for activities were significantly lower than residents in nursing homes [11]. Forty-two per cent of Australians referred to home care screened positive for depression [12], and similarly 43% of American home care clients met DSM-IV criteria for depression [13]. Sixty per cent of community dwelling persons with dementia have behavioural disturbances [14]. These behaviours such as agitation, aggression, psychosis, anxiety and depression are stressful and increase the burden of carers, and increase the likelihood of institutionalisation [15].

Psychosocial activity-based interventions, particularly tailored activities, have been shown to improve outcomes for residents in aged care facilities and are recommended in many dementia management guidelines [16,17]. For instance, music and diversional therapy decrease depression, anxiety and social withdrawal for persons with dementia [18]. Aromatherapy, preferred music, muscle relaxation training, Montessori activities and humour therapy have been shown to reduce behavioural disturbances in agitation, aggression and verbal disruption [19-21]. Individualised activity programs tailored to older person’s cognitive, physical, and sensory abilities, and their lifelong habits and roles have been particularly effective in decreasing agitation, depression and improving quality of life of persons with dementia [22]. Common to these interventions is engagement of clients, which may fulfil unmet needs for company or meaningful activity and stimulation [23]. We believe that engagement of residents through activity is the critical ingredient for these interventions.

Only a few tailored psychosocial activity programs have been trialled in community settings for people with dementia [24,25]. All involved use of experienced therapists in addition to existing care. A 10 session in-home program conducted by occupational therapists included environmental modification, and training for patients and carers on how to optimise functional performance. This program reported improving the mood and quality of life of persons with dementia [25]. The Tailored Activity Program (TAP) showed that assessment informing tailored activity prescription by an occupational therapist coupled with caregiver training over eight sessions at home reduced problem behaviours and increased pleasure and engagement of persons with dementia [24]. TAP costs $961.63 per caregiver-client dyad and sustainability of effects is not known as there was no follow-up beyond four months [25].

The aim of this study is to evaluate the effects of LEAP for life on increasing home care client engagement by aged care staff. The effects of the program on client mood, behaviour and satisfaction with care, and care worker satisfaction with work will also be measured.

## Methods/design

The design of the program was informed by Greenhalgh’s framework for diffusion of innovations in service organisations [26] and the literature on implementation and culture change in health and aged care [27-35]. Cost, scalability and sustainability were also considerations of the program design. We did not specifically base the program design on a theory, as there was no published theory that appeared suitable with a sound evidence base in predicting good implementation outcomes [36]. The three components of the program are:

1) Engaging site management and care staff with the LEAP for Life program

2) Employing a LEAP champion one day a week at each site

3) A training program (detailed below)

The program logic model of the implementation is outlined in Figure 1. LEAP will encourage case managers to include social and recreational goals in client care plans; and care workers to increase behaviours which engage clients socially and recreationally. Behavioural change of care workers and case managers is to be driven by a LEAP champion within each site. By increasing client engagement, we hypothesise that client depression, loneliness, apathy and/or agitation will improve for those with symptoms in these areas, and that satisfaction with care will also increase. We also hypothesise that relationships between care staff and clients, and care staff work satisfaction will increase.

**Figure 1 F1:**
[figure not shown]
LEAP for life program logic model.

A position description has been written for the LEAP champion and champions will be selected after discussion with site managers. The role of the LEAP champion is to: support care workers in ways to meaningfully engage clients; assist case managers in including social or recreational goals within clients’ care plans; develop personalised resources for client engagement; develop an activities library; accompany care workers on buddy shifts; and to liaise with the research team.

### Development of the training sessions

The training sessions have been developed based on literature reviews and consultation with experts as detailed under each training component below. We also reviewed the literature on how to best deliver training for aged care workers [37-39], and drew on the experience of the Advisory and Steering committee. The training program was designed around the principles that it was to be interactive, practical and skills based; allow care staff to experience the impact of the psychosocial strategy; include self-reflection and discussion; acknowledge care staffs’ expertise and experiences; take a problem solving approach; inspire; and be fun. The training program was also developed to cater for staff with different levels of education, English language proficiency and cultural backgrounds [40].

Barriers to implementing lifestyle activities in home care were identified through the advisory and steering groups and from -6 month interviews with case managers at participating sites. Barriers identified were: lack of time, lack of knowledge, lack of resources, and attitudes of families and clients that the remit of the care worker is to just provide practical or physical assistance. These have been explicitly addressed in the training and practice change program.

The training program structure is outlined in Table 1. Each training session was refined using feedback from the advisory group, steering committee, and following a pilot session at a non-participating service.

**Table 1 T1:** LEAP for life training program lesson topics, learning objectives, activities and duration

**Training lesson topic**	**Learning objectives**	**Training activities**	**Time (hours)**
Case Manager			
Introduction to LEAP and goal setting with clients	• To understand why the LEAP for Life program is important	1. Introduction of facilitator/s and ground rules	3
	• To learn SMART social and recreational goal setting skills	2. Icebreaker –where key life moments are shared to emphasise the importance of socialisation and recreation	
	• To learn how to select and modify goals for community aged care clients in relation to their cognitive and functional ability	3. LEAP for Life within a community aged care context: a) Maslow’s hierarchy of needs b) the importance of LEAP b) how to implement LEAP in community aged care	
	• To learn how to incorporate social and leisure goals into current care plans with community aged care clients	4. Workshop as a group a) setting a SMART goal, and b) setting SMART goal sub-steps	
	• To explore ways of and barriers to, implementing the skills and strategies learnt in training, into their usual practice	5. Role play in pairs setting SMART goals with clients	
		6. Brainstorm as a group how to maximise implementation and sustainability of LEAP within own organisation	
		7. Self-reflection activity on what each person will put into practice from the session	
Care worker			
Introduction to LEAP, communication skills, engaging clients and reminiscence	• To understand the importance of engaging and supporting clients through socialisation and recreation	1. Introduction of facilitator/s and ground rules	3
	• To understand the purpose of the LEAP for life program, and program structure	2. “Whoosh” ball game icebreaker: a physical group activity to get the group engaged, comfortable and having fun	
	• To understand that goal setting with clients will occur, and how they may contribute to achieving goals	3. Brainstorm as a group the care workers role and what care workers like/dislike about their job	
	• To understand how to involve and engage clients more during usual care	4. Overview of LEAP for Life: a) the program logic model b) an understanding that goal setting with clients will occur	
	• To improve listening skills using body language and questioning	5. Brainstorm as a group the benefits of keeping active	
	• To understand the principles of reminiscence	6. Brainstorm as group how to involve clients more during usual care activities	
		7. Communication skills pair work exercises: a) the importance of good body language b) active listening – paraphrasing, reflecting, mirroring, paying compliments	
		8. Brainstorm as a group how to get people talking and play “six degrees of separation” game in pairs.	
		9. Brainstorm as a group how to encourage clients to reminisce	
		10. Group discussion about what to do when the conversation goes wrong	
		11. Self-reflection activity on what each person will put into practice from the session	
Engaging clients with dementia	• To revise previous session behavioural and psychological symptoms of dementiaTo understand the	1. Introduction of facilitator/s and ground rules	2
	• To develop skills on communicating with people with dementia	2. Group discussion about strategies learnt or practiced last session	
	• To develop skills on task analysis	3. “Whoosh” ball game icebreaker: a physical group activity to get the group engaged, comfortable and having fun	
	• To develop skills in using Montessori principles to present and tailor activities for people with dementia	4. Dementia: a) an understanding that people with dementia may express challenging behaviour because of an unmet need or changes in the brain b) an understanding that LEAP for Life may help to address unmet needs	
		5. Brainstorm as a group good practices when communicating with people with dementia	
		6. Broken Telephone activity to demonstrate the importance of clear and slow speech and “looking” for feedback	
		7. Balloon modelling mirroring activity to demonstrate the value of modelling rather than describing a task	
		8. Brainstorm as a group task analysis and modification of making a cup of instant coffee	
		9. Montessori Principles: a) introduction, b) sorting activity demonstration with cutlery c) group brainstorm as to other activities one might be able to do around the house with a client with dementia d) role play in pairs turning a household object into an activity with a person with dementia	
		10. Self-reflection activity on what each person will put into practice from the session	
Incorporating music and physical activity into daily care	• To revise previous session	1. Introduction of facilitator/s and ground rules	2
	• To understand and experience the benefits of music	2. Group discussion about strategies learnt or practiced last session.	
	• To learn how to select and incorporate into daily care individualised music for clients	3. “Name that song” group activity to experience the enjoyment and reminiscence effects of music	
	• To learn how to encourage a person with dementia to actively engage with music	4. Brainstorm as a group how to select music with and for clients and for different moods	
	• To understand the benefits of physical activity	5. Brainstorm as a group how to incorporate music into daily care with clients	
	• To learn how to incorporate physical activity into daily care	6. Group singing activity to give care workers confidence in singing and to experience the benefits of engaging in music with others	
	• To learn about activities and approaches that might be most suited to engaging male clients	7. “Follow my leader” paired activity to practice encouraging people with dementia to move along to music	
		8. Brainstorm as a group activities and approaches most suited to engaging male clients	
		9. Facts about exercise trivia quiz to emphasise benefits of physical activity	
		10. Brainstorm as a group how to encourage clients to be physically active	
		11. Self-reflection activity on what each person will put into practice from the session	
Humour and play and status and reciprocity	• To revise previous session	1. Introduction of facilitator/s and ground rules	2
	• To understand what play and humour are and their benefits	2. Group discussion about strategies learnt or practiced last session	
	• To understand appropriate and inappropriate play and humour	3. Chair swap circle game: a physical group activity icebreaker to get the group engaged, comfortable and having fun; and to experience the playful approach important in initiating a playful encounter	
	• To develop skills to be more playful with clients	4. Group discussion about what play is, and the difference between a playful activity and a playful state	
	• To develop problem-solving skills and creativity	5. Brainstorm as a group the social, emotional and physical benefits of play	
	• To explore barriers to play and humour with clients	6. Group discussion about using play at work focused on promoting the understanding that being playful at work will increase creativity, and in turn improve problem-solving ability	
	• To understand and develop strategies for increasing the status of clients	7. Circle drawing activity to practice thinking creatively	
	• To identify practices to maximise sustainability of LEAP within organisation	8. Group problem-solving exercise about a hypothetical challenging client to practice applying creative thinking to work problems	
		9. Group discussion about Marin’s four distinct styles of humour, and self-reflection on own humour style	
		10. Brainstorm as a group ways to be more playful and humorous with clients	
		11. Brainstorm as a group risks and barriers of being playful with clients	
		12. Group discussion about the concept of status and the loss of status in older people	
		13. Brainstorm as a group ways to increase the perceived status of clients	
		14. Group reflection about the skills care workers have learnt over the course of the LEAP training program	
		15. Brainstorm as a group ways in which the care organisation can maximise the sustainability of LEAP	
LEAP Champion			
The LEAP Champion role, organizational change and interpersonal skill sin person persuasion	• To get to know other LEAP champions and form a collaborative network;	1. Introduction of facilitator/s and ground rules	5
	• To be clear about LEAP champion role within own organisation;	2. Icebreaker – getting to know the other LEAP Champions and finding out three things each has in common	
	• To anticipate difficulties in promoting change within organisation and brainstorm solutions;	3. Brainstorm as a group the LEAP Champion role	
	• To improve interpersonal skills in person persuasion – active listening, constructive feedback, negotiation, assertiveness, and persuasion;	4. The change process: a) Roger’s diffusion of innovations process, b) Roger’s adopter categories	
	• To define how LEAP will work in each individual’s own schedule and organisation.	5. Brainstorm as a group what characteristics and skills the LEAP Champion will ideally have	
		6. Self-reflection exercise on each individual’s strengths and challenges in regards to the LEAP Champion role	
		7. Communication and Influencing Skills: a) good listening pair work exercise b) giving feedback – pair work exercise using the sandwich technique c) assertiveness skills group role-play d) negotiation tactics and persuasion tips e) persuasion skills pair work exercise	
		8. Groups discussion about the buddy shift	
		9. Individual exercise planning how each LEAP champion will manage their one work day of LEAP	
		10. Brainstorm as a group how UNSW will support the LEAP champions in their role	
		11. Self-reflection activity on what each person will put into practice from the session	

### LEAP champion training

One five-hour champion training session informed by the literature [41-44], will be delivered three months prior to the start of the program. The training will clarify the LEAP champion role including specific tasks to be performed, educate LEAP champions in the process of change and responses to change; develop interpersonal skills for person persuasion; identify potential difficulties and brainstorm solutions within their sites; and encourage networking between the LEAP champions.

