### Design

LEAP is being evaluated using a quasi-experimental design with measurements taken at -6, 0 (baseline immediately pre-intervention), 6 and 12 months. The time period from -6 to 0 months will act as non-intervention comparison for the period between 0, 6 and 12 months. Clients will be clustered under their case managers (*n* = 20).

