## Discussion

LEAP for Life is a pragmatic program with the aim of increasing engagement of aged care clients by aged care staff. The program is designed to be economical to deliver and self-sustaining after the implementation period, and is being evaluated in the real world setting.

The non-controlled design means that we cannot with certainty attribute any observed changes to the LEAP program. However it is unlikely that care worker behaviour with relation to clients would systematically be affected by external factors. The detailed process evaluation will also add confidence in attributing the change to the implementation processes, as well as in understanding the mechanisms and processes involved in changing home care staff behaviour.

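### Champion training is scheduled at month -3, inside the -6 to 0 month window that serves as the trial's only non-intervention comparison; early champion activity could pull the slope difference towards no effect

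*Protocol article*

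**What the plan says.** **Timing of the waves.** The abstract places the four data collections "6-months prior to program commencement; at the start of the program; and then after 6 and 12 months". The Design section gives "measurements taken at -6, 0 (baseline immediately pre-intervention), 6 and 12 months". Month 0 is therefore both programme start and the last assessment before intervention.

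**The comparison.** Under Design: "The time period from -6 to 0 months will act as non-intervention comparison for the period between 0, 6 and 12 months". The Data analysis section estimates one slope from -6 to 0 months and another from 0 to 12 months, and tests their difference at two-sided 0.05. There is no concurrent control.

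**The champion.** The LEAP champion training section says: "One five-hour champion training session informed by the literature [41-44], will be delivered three months prior to the start of the program". That is month -3. Methods/design lists "Employing a LEAP champion one day a week at each site" as the second of three programme components, and says that the champion is to drive behaviour change among care workers and case managers. The champion session is also a row of Table 1, which sets out the training programme.

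**Other delivery.** Case managers are trained when the programme begins (Case manager training). Buddy visits take place during the training programme (Care worker training). The remaining champion tasks, described below Figure 1, carry no start date: supporting care workers, helping case managers with goals, and building resources and an activities library.

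**The concern.** The primary test asks whether engagement improves faster after month 0 than before it, so the -6 to 0 month slope stands in for what would have happened without LEAP. One programme element is delivered halfway through that period, to the people named as the drivers of change. According to Table 1, the session covers persuasion and negotiation skills, has each champion plan their LEAP working day, and closes with what each will put into practice.

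If champions act on this before the month-0 assessment and engagement rises, the pre-slope and the month-0 mean both rise. The test then subtracts part of the programme's own effect. The pre-slope rests on two waves with none at month -3, so an early champion effect and a background trend would look alike in the outcome data. A null result could not then be cleanly told apart from programme failure.

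**Working it through.** **The plan's own figure.** The Power section claims at least 80% for a one-group pre-post comparison with n = 211, d = 0.2, rho = 0.5 and two-sided 0.05. Power = Φ(d√n / √(2(1 - rho)) - 1.96) = Φ(0.2 × 14.526 / 1 - 1.96) = Φ(0.945) = 82.8%. The claim reproduces and does not depend on the present point. The documents give no figure for early champion effects, so everything below is expressed in terms of unknowns.

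**Step 1: contrast weights.** Times are -6, 0, 6 and 12 months with a knot at 0. Assuming equal correlation between waves (least squares gives the same result), the slope difference per 6 months has weights

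(1, -4/3, -1/3, 2/3).

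The month-0 weight is negative, so a higher month-0 mean lowers the estimated effect.

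**Step 2: bias from an early gain g seen at month 0.**
- Transient, pattern (0, g, 0, 0): -4/3 × g = -1.33g.
- Persistent, pattern (0, g, g, g): (-4/3 - 1/3 + 2/3)g = -1.0g.

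The persistent pattern lies exactly on the piecewise line, so its value does not depend on the correlation assumption. The transient value does.

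**Step 3: attenuation as a share of the programme effect.** Let S be the true programme gain per 6 months. Let improvement start at month -3 at a fraction f of that rate. The gain by month 0 is e = 0.5fS. The fraction f is an assumption.
- Later gain continues at the full rate: pre-slope e, post-slope S, difference S - e = S(1 - 0.5f).
- Month-12 level is fixed at 2S, so early gain uses up later gain: pre-slope e, post-slope (2S - e)/2, difference S - 1.5e = S(1 - 0.75f).

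| f | Loss, gain continues | Loss, month-12 level fixed |
|---|---|---|
| 0 | 0% | 0% |
| 0.1 | 5% | 7.5% |
| 0.25 | 12.5% | 18.75% (about 19%) |
| 0.5 | 25% | 37.5% |

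Both patterns also lie on the piecewise line, so these losses hold for any correlation structure.

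**Step 4: illustration on power.** Assume a linear gain of 0.4 SD by month 12, n = 211, SD 1, rho = 0.5 between all waves and no allowance for clustering. Power of the slope-difference test is 61% at f = 0. It is 57% or 55% at f = 0.1, 50% or 45% at f = 0.25, and 39% or 29% at f = 0.5 (gain continues, or month-12 level fixed). Only the drop from the f = 0 value bears on this point.

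**The case against.** The best defence is that the session is preparation and not delivery. It is five hours for the champions of five sites. Its content is role, change process and interpersonal skills; the client-facing techniques (reminiscence, Montessori activities, music, play) belong to the care worker sessions. The abstract makes the champion's weekly day a component of a 12-month programme, which suggests that the day belongs to months 0 to 12. Case managers are not trained in goal setting until the programme begins, so champions have little to support before then. Any early effect would have to pass from champion to untrained staff to client scores within three months, and no section describes that. All of this stands, and it makes a small f plausible.

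The process evaluation also helps. Case managers are interviewed at each time-point, champions have monthly phone meetings, care plans are audited, and process data may be used as predictors of outcome. Early activity could therefore be noticed, though not cleanly separated from a background trend. The article does not say whether the monthly calls begin before month 0.

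Finally, the Discussion concedes: "The non-controlled design means that we cannot with certainty attribute any observed changes to the LEAP program". That concession covers the missing control. The argument that follows it discounts external influences and does not address the programme's own activity inside the comparison window.

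What the defence does not remove is the stated conflict: a listed programme element falls inside a period labelled free of intervention, and no sentence holds the undated champion tasks until month 0.

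**Conclusion.** The timing conflict is real and stands in the text. It touches the only comparator of the primary test, so it should be fixed, but it does not invalidate the design. If early activity raises engagement, the bias runs towards no effect, so it would not by itself create a false claim of benefit. An early worsening would push the other way. The loss is 0% if champions have no effect before month 0 and 5-7.5% at f = 0.1, rising to 25-37.5% at f = 0.5. The documents do not say where in that range the trial would fall.

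A reader might infer three stronger things that the documents do not support.
- **That contamination will occur.** Nothing shows this, and the placement of most hands-on delivery argues for a modest effect at most.
- **That half or more of the effect is lost.** An early gain of 0.05 SD set against 0.1 SD per 6 months gives 50-67% (0.05/0.1 and 1.33 × 0.05/0.1). But that gain equals f = 1, the full programme rate running from month -3 (0.5 × 1 × 0.1 = 0.05). The benchmark also assumes that d = 0.2 applies at 12 months, which the Power section does not say. If d applied at 6 months, the same gain would give 25-33%.
- **That the problem would be undetectable.** The process data could show whether early activity took place, even though the outcome data alone could not isolate its effect.

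**What to change.** Reconcile the LEAP champion training and Design sections in one of these ways.

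1. Hold champion training after each site's month-0 assessments are complete.
2. Keep the date, but state that champions begin no LEAP activity with staff or clients until those assessments are complete. Record any early activity through the planned champion phone meetings, starting them from the date of training.
3. If neither is feasible, remove the non-intervention label from the -6 to 0 month period and state that early champion activity would probably bias the slope difference towards no effect.

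The cost is an instruction to the champions at five sites and a sentence in Design. The first option leaves champions slightly less lead time. The second keeps the lead time but depends on compliance, which is why it needs the record.
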